## Methods

### NMES protocol

To assess spinal motor control network excitability, we will apply NMES on the extensor carpi radialis (ECR) and/or flexor carpi radialis (FCR) during the HMI movement task. The applied NMES will trigger H-reflex in the muscle and resultant MEP will be captured using the Trigno Avanti EMG sensors with two sensors placed on the ECR and two on the FCR muscles. The location of the ECR is found by using a motor map derive from a cursor pixel/EMG relationship as shown in Figure 2. Similarly, the muscle belly is identified by having the subject place their forearm down on a flat surface with their palm down, then extending their wrist towards the thumb and back. The FCR is found by using the motor map, and/or having the subject place their forearm on a flat surface with their palm up to identify the muscle belly. To do so, the subject brings their thumb to their middle finger and flexes their wrist so their fingers point to their elbow. While the subject is in the flexed position the contracted muscle belly is found by touching the muscle. The NMES will be applied over two channels (one for ECR and one for FCR) and will be produced using a Hasomed RehaStim in Sciencemode controlled via Labview (settings—Baudrate: 115200; Data Bits: 8; Parity: None; Stop Bits: 2; Flow Control: CTS). Labview triggers the stimulation when the cursor begins entering the target area. Stimulation levels are determined using a ramp up, initially, with a 5 mA amplitude 250 μs pulse, and then incremented by 5 mA until reaching the individuals maximum comfort range. For repeated NMES, we use an amplitude that is 85% of that maximum (although some may require higher for a more profound effect). To verify the NMES triggered MEP, the stimulation should evoke a contraction that is at least 25–30% of a maximum voluntary contraction (54) as measured using the HMI which minimizes the likelihood of a startling effect.

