**Figure 3 fig3:**
[figure not shown]
NMES impulse pathway. NMES typically first triggers the sensory-afferent pathway, then affects the homonymous efferent pathway to generate a MEP. The spinal-muscle section in this mode is shared with the feedforward TMS triggered pathway, but does not share the descending brain-spinal cord network elicited through TMS.

Additionally, the NMES impulse at the spinal-level creates a secondary measurable dynamic response. NMES applied at the muscular level triggers direct motor response (M wave) and/or a closed-loop afferent-spino-muscular response (NMES ➔ muscle) that captures the neural dynamics related to the motion (also see Appendix) (38). For example, M1 issued motor commands are a feed-forward representation of the movement strategy, thus by perturbing only the spinal-level motor controller the cortical feed-forward mechanisms remain intact, but spinal-level computations are altered. It is important to note that although the afferent-to-efferent pathway shown in Figure 3 includes the sensory-motor feedback loop in the motor controller, the NMES triggers short latency neuromuscular stimulation in a feedforward matter (i.e., direct path from NMES to muscle stimulation) and thus does not represent a closed loop mechanism. The true feedback response comes after the initial NMES stimulation (M wave), following spinal or cortical level processing (H-reflex or F wave). Additional information on the behavior of these mechanisms can also be found in our earlier computational studies of the corticospinal system (4, 67–69). The NMES thus provides impulse-response dynamics of short-latency sensory-modified motor control strategies irrespective of cortical driven movement formation (70).

In terms of the system response, the dynamic control motor outputs, MO, of these pathways are defined using standard representative systems:

(1)
$$MO_{TMS}=M\left(s\right)CP\left(s\right)R_{TMS}\left(s\right)$$

(2)
$$MO_{NMES}=M\left(s\right)SP\left(s\right)R_{NMES}\left(s\right)$$

Where, R is the input function. Individually these system representations denote their unique stimulation-response pathways, e.g., cortico-muscular or spinal-muscular, CP is the cortical pathway, SP is the spinal pathway, as shown in Figures 3, 4. If both pathways are known through application of TMS and NMES, their relative contributions can be discovered mathematically such that:

(3)

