Thus Equation 7 shows that the spinal-level isolated impulse-response, SP(s), can be measured by comparing the response characteristics due to TMS and NMES. Similarly, Equation 9 shows that the cortical-level isolated impulse-response, CP(s), can also be measured in a similar way. However, what is important to identify as part of these equations that the muscle pathway motoneuron effect, M(s), is removed. This reduces controller block sizes, and separates the cortical and spinal functionality before motor execution. In other words, the unshared portions of the neural impulse-responses can be investigated [CP(s): brain to spinal cord pathway; and SP(s): afferent sensory pathway]. This is novel in that the complexity of delineating cortical and spinal systems is exceptionally difficult due to their shared endpoint networks. Based on our earlier studies, these computational representations of the complex non-linear motor controller have been validated with similar NIBS based studies measuring motor response times (4, 67–69). Specifically, although a linear approach is taken above, the components of the system are highly non-linear and have shown a robust ability to emulate the corticospinal motor controller.

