### Expected outcomes

The development of this presented neurostimulation method is part of a larger study that aims to create the first corticospinal model of the neuromuscular controller. As a result, using our blended protocol we will achieve two representations of the motor controller, its issued commands, and their dynamic responses using TMS (along with cortically modulated TMS via tDCS) and NMES. These measured behaviors will thus give us impulse-response behaviors of long latency feed-forward neuromuscular systems (cortico-muscular pathway) as well as short-latency feedback control modifications (spino-muscular pathway) in the motor task. Used jointly, the blended method provides a tool to probe the neuromuscular system and to determine brain- and spinal-level contributions to motor control. However, what is more, is that these impulse-response dynamics will be person-specific, and response dynamics will change over time with motor learning. For example, the M1 issued feedforward control will change over time as an individual learns a task or through tDCS neuromodulation (71), and thus the impulse-response generated via TMS will change to reflect that (72). Similarly, spinal-level NMES impulse-dynamics measure changes in spinal network topologies during motor learning independently of cortical level learning (73).

In the short term we will apply this blended method on healthy subjects to explore variation in cortical- vs. spinal-level relative contributions, and how it changes longitudinally with time. What we expect to find is that as an individual becomes more adept at a motion task, the interconnection of corticospinal pathways will change; e.g., increased corticospinal functional connectivity (74). So, with motor learning the feedforward M1-Muscle pathway will be more pronounced in learning motion behaviors, as sensory dependencies decrease in motor command formulation under these conditions (75).

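### SP(s) is defined in two ways, so a change in spinal motoneuron excitability may be counted in SP(s) or in the shared factor M(s), and with CP > SP the two readings move Equation 5 in opposite directions

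*Protocol article*

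**What the plan says.** All references are to the protocol article.

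- **The blended NIBS-NMES method, after Equation 2:** "CP is the cortical pathway, SP is the spinal pathway". The text after Equation 5 likewise treats SP(s) as the command from the spinal level.
- **Same section, Figure 3 caption:** "The spinal-muscle section in this mode is shared with the feedforward TMS triggered pathway".
- **Same section, after Equation 9:** "the spinal-level isolated impulse-response, SP(s), can be measured by comparing the response characteristics due to TMS and NMES". The paragraph adds that "the muscle pathway motoneuron effect, M(s), is removed", and names what is left as the unshared portions: "CP(s): brain to spinal cord pathway; and SP(s): afferent sensory pathway".
- **NMES protocol:** the purpose of NMES is given as "To assess spinal motor control network excitability".
- **Expected outcomes:** "spinal-level NMES impulse-dynamics measure changes in spinal network topologies during motor learning". The same section predicts that CP(s) − SP(s) will rise during recovery, as in healthy learners, and points to Equation 5 for that contrast. Equation 5 still contains M(s).

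**The concern.** The wide and the narrow definitions of SP(s) are different quantities. The narrow one leaves out the output side of the cord. If that side is part of the section shared with TMS, it belongs to M(s), because M(s) is the only pathway factor that Equations 1 and 2 have in common.

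The article's purpose is to separate cortical from spinal contributions and to follow them through learning or after stroke. If one physiological change can be booked in either of two terms, and the booking decides which way the tracked contrast moves, that contrast has no fixed meaning. The risk runs towards the hypothesis: with CP > SP, a rise in excitability of the shared section enlarges Equation 5 and looks like the predicted gain in the feedforward pathway.

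**Working it through.** **Inputs.** Equations 1, 2, 5, 7 and 9 are taken as written, with the input R normalised to 1. The article gives no values for M, CP or SP. The gains below are assumptions: positive scalars, M = 1.0, CP = 1.0, SP = 0.6.

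**Step 1: what the equations reduce to.** By Equation 3, MO_TMS − Δ_MC = MO_NMES. Equation 7 is therefore SP = MO_NMES/(M·R), and Equation 9 is CP = MO_TMS/(M·R). M(s) leaves these expressions only if its value is known and divided out.

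**Step 2: baseline.** MO_TMS = 1.0 × 1.0 = 1.00. MO_NMES = 1.0 × 0.6 = 0.60. Equation 5 = 1.0 × (1.0 − 0.6) = 0.40.

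**Step 3: a 20% spinal rise under each reading.**

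| Quantity | Baseline | Rise in M (M = 1.2) | Rise in SP (SP = 0.72) |
|---|---|---|---|
| MO_TMS | 1.00 | 1.20 | 1.00 |
| MO_NMES | 0.60 | 0.72 | 0.72 |
| Equation 5 | 0.40 | 1.2 × 0.4 = 0.48 | 1.0 − 0.72 = 0.28 |
| SP, true M divided out | 0.60 | 0.60 | 0.72 |
| CP − SP, true M divided out | 0.40 | 0.40 | 0.28 |
| MO_TMS/MO_NMES | 1.67 | 1.67 | 1.39 |

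A 20% fall in M gives 0.8 × 0.4 = 0.32 in Equation 5. If M rises to 1.2 but the baseline value of 1.0 is divided out, the estimates become SP = 0.72 and CP = 1.20, so the change leaks into both.

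**Step 4: how far the reversal depends on the gains.** For a rise by a fraction k, Equation 5 changes by +k·M(CP − SP) if the rise is in M, and by −k·M·SP if it is in SP. The signs are opposite whenever CP > SP > 0. With CP = 0.8 and SP = 0.5, Equation 5 goes from 0.30 to 0.36 or to 0.20. With CP < SP both changes are negative: for CP = 0.6 and SP = 1.0, −0.40 goes to −0.48 or to −0.60.

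**Step 5: can the data tell the readings apart?** Only in part. There are two outputs and three unknowns. Outputs of 1.20 and 0.72 fit M = 1.2, CP = 1.0, SP = 0.6, and fit M = 1.0, CP = 1.2, SP = 0.72 equally well. A change that leaves MO_TMS/MO_NMES constant can be recognised as parallel, but the equations cannot say whether it lies in M or equally in CP and SP.

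**The case against.** A reader might infer that spinal change cannot appear in any outcome of this protocol. The documents do not support that, for three reasons.

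- Equations 2 and 5 both keep M(s), so a motoneuron change does reach the NMES output and the Equation 5 contrast.
- The statements on spinal excitability (NMES protocol) and network topology (Expected outcomes) concern the NMES response and do not mention SP(s). A motoneuron change appears in the quantity they name.
- Nothing says that all spinal processing lies in M(s). Processing on the afferent side of the motoneuron may remain in SP(s).

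There are further fair points. Equation 2 already keeps M(s) apart from SP where SP is first named, so the later wording may be loose labelling of the remainder and not a second model. Placing the whole section from cord to muscle in M(s) is an inference from a caption and from the form of the equations; the drawings in Figures 3 and 4 and the Appendix are not available to check it. The text after Equation 5 says openly that the measured difference is only proportional to CP − SP. Study limitations admits that the equations are simplified and that separability is incomplete.

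These points rule out the strong reading and make the size illustrative. They do not remove the inconsistency. The limitations section does not say which definition applies or which quantity reports spinal excitability, and a proportionality factor that can itself change over time is exactly what makes a longitudinal reading of Equation 5 ambiguous.

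**Conclusion.** The point holds as an inconsistency in the definition of a core estimated quantity, with a consequence for interpretation. As written, a change in spinal motoneuron excitability may belong to SP(s) or to M(s). If to M(s), it disappears from an SP(s) with M(s) truly removed but scales Equation 5, the expression cited for the predicted longitudinal rise.

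In the worked example the same 20% rise gives +0.08 or −0.12 on a baseline of 0.40. These sizes rest on assumed scalar gains. The opposite directions need only positive gains with CP > SP. The placement in M(s) rests on the Figure 3 caption and the form of Equations 1 and 2.

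The article should be corrected on this point, since it affects what the study can conclude about cortical against spinal change.

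**What to change.** 1. Use one definition of SP(s) throughout. If the narrow one after Equation 9 is kept, describe SP(s) as the afferent limb after Equation 2, after Equation 5, in the sentence interpreting Equation 7, and where Expected outcomes refers to CP(s) − SP(s).
2. State that spinal excitability and network change, as named in NMES protocol and Expected outcomes, are read from the NMES output, which includes M(s).
3. When the TMS and NMES outputs change by the same proportion, do not interpret a change in Equation 5 as a change in CP − SP. Report that pattern as compatible with a change in the shared section M(s) or with an equal proportional change in CP and SP, because the equations cannot separate these. Assigning it to M(s) alone would claim too much.

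The cost is wording plus one simple summary of the proportional change in each output. The downside is a narrower claim about isolating spinal-level contributions.

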### Expected outcomes

The development of this presented neurostimulation method is part of a larger study that aims to create the first corticospinal model of the neuromuscular controller. As a result, using our blended protocol we will achieve two representations of the motor controller, its issued commands, and their dynamic responses using TMS (along with cortically modulated TMS via tDCS) and NMES. These measured behaviors will thus give us impulse-response behaviors of long latency feed-forward neuromuscular systems (cortico-muscular pathway) as well as short-latency feedback control modifications (spino-muscular pathway) in the motor task. Used jointly, the blended method provides a tool to probe the neuromuscular system and to determine brain- and spinal-level contributions to motor control. However, what is more, is that these impulse-response dynamics will be person-specific, and response dynamics will change over time with motor learning. For example, the M1 issued feedforward control will change over time as an individual learns a task or through tDCS neuromodulation (71), and thus the impulse-response generated via TMS will change to reflect that (72). Similarly, spinal-level NMES impulse-dynamics measure changes in spinal network topologies during motor learning independently of cortical level learning (73).

In the short term we will apply this blended method on healthy subjects to explore variation in cortical- vs. spinal-level relative contributions, and how it changes longitudinally with time. What we expect to find is that as an individual becomes more adept at a motion task, the interconnection of corticospinal pathways will change; e.g., increased corticospinal functional connectivity (74). So, with motor learning the feedforward M1-Muscle pathway will be more pronounced in learning motion behaviors, as sensory dependencies decrease in motor command formulation under these conditions (75).

Later, we will apply this new method as part of a clinical-based study to explore motor re-learning for neurorehabilitation. Patients participating in the study will undergo this protocol in at least three milestones of their neurorehabilitation protocol: (a) Immediately following stroke, at the start of the treatment; (b) at an approximate half-way point during their rehabilitation plan; and (c) at the end of the neurorehabilitation plan (either in a clinical or at-home setting). We will use the blended neurostimulation protocol to measure changes to the neuromuscular controller from baseline, and track their progress over time. By measuring impulse-response dynamics of the corticospinal system, we will identify how these control pathways change—specifically, how they issue motor commands during re-learning—over time. We expect, much like with healthy subjects, there will be an increase in the feedforward pathway such that CP(s)—SP(s) (see Equation 5) becomes more positive. We also expect to see that the peak MEP variability associated with TMS impulse decrease over time as reported in earlier studies. Inter-test repeatability is inconsistent across NIBS studies, but it has been shown that the variability decreases with repeated stimulation and/or neuromodulation (not necessarily the peak amplitude of the MEP) (76). This coincides with what we expect in motor learning, since as the feedforward controller improves, less internal variation will occur in the issued motor command and subsequently less emphasis given to sensory-driven command formulation.

Ultimately, this new method gives clinicians and scientists a unique template to understand variable across populations, changes in individuals over time based on motor learning, and allows healthy and diseased states to be classified cross-sectionally.

### Study limitations

Some of our suppositions of the measured impulse responses of the system are simplified representations such as in Equations 1–9. In reality, the corticospinal system is a highly non-linear network that cannot be represented by simpler linear time-invariant representations. However, although the computational approach is linear, the components of the system are non-linear and mimic corticospinal systems (such as a sigmoidal function that represents the cortico-muscular pathway). This is supported by our earlier study that explored how NIBS affects motor response times (4). In addition, although we assume the separability of the data is possible, we do not completely assume that the dynamic responses are entirely deconvolute. Instead, we posit that the separability of the system will be measurable and specifically the dynamic response and proportional outcomes measured though TMS or NMES are representative of the changes to those neural networks. We also do not explicitly state this as a final solution to the problem, but instead the first representative step to create tangible methods that can be used to fully investigate the corticospinal system.

## Data availability statement

The original contributions presented in the study are included in the article/Supplementary material, further inquiries can be directed to the corresponding author.

